**Methods:**

This investigator-initiated prospective randomized monocentric controlled trial is designed to randomly allocate 200 patients undergoing elective primary total joint arthroplasty of hip or knee to one of two groups as follows: Group C (control group) – peripheral venous cannula insertion by palpation or Group USG (intervention) – cannula insertion by ultrasound-guided vascular access. Our primary endpoint is to compare the number of attempts for ultrasound-guided insertion of the peripheral venous cannula with common palpation insertion of the peripheral venous cannula in overweight/obese patients (BMI ≥ 25). The secondary endpoint is a failure rate of the peripheral venous cannula to administer intravenous therapy up to 5 days postoperatively. Tertiary endpoints include a portion of long PVCs that are able to ensure blood draw up to 5 days postoperatively, time needed to insert PVC in each group, number of needle tip redirections in both groups, and reinsertion of PVC needed in both groups for any reason.

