### Outcomes {12}

In order to achieve primary and secondary outcomes, the number of attempts, number of cannulas used, tip redirections, time needed to insert the cannula, and proportion of cannulas that requires reinsertion, all this is recorded in the study protocol (Fig. 2) during the procedure. Then researchers will compare both groups to each other. These outcomes are crucial to determine clinical efficacy not just on insertion, but to compare the service life of the cannula inserted. The lifespan of the cannula is related to site of insertion (flexion point), damage to the vessel wall (number of redirections, 1^st^ pass), and proportion of cannula width to vessel diameter. Risks of peripheral vein cannulation are well known and, in general, considered minor.

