## Statistical methods

### Statistical methods for primary and secondary outcomes {20a}

The primary and secondary outcomes will be evaluated using the *χ*^2^ test in terms of the difference in approaches of cannula insertion between groups in the number of punctures and the failure rate of the cannulas (failure rate is defined as the proportion of cannulas requiring reinsertion within 5 days after insertion). RR and 95% confidence interval of successful venous cannulation will be also calculated. The primary endpoint is the number of attempts to successful cannulation determined by the number of skin punctures. More attempts are associated with complications. As a secondary endpoint, the failure rate is calculated from the ratio of cannulas that did not fail to cannulas that failed for any reason in each group, up to the first 5 days postoperatively. This data is obtained from the patient protocol (Fig. 2). Primary and secondary outcomes will be reported as frequencies and percentages. For our tertiary outcome, to compare differences between the intervention groups (time required for cannula insertion, number of cannulas used, A-DIVA scoring system, etc.), *t*-test for independent groups or Mann–Whitney U test will be used, if data are not normally distributed. The effect of the intervention on outcome variables will be determined by using paired *t*-test or Wilcoxon signed-rank test for data obtained at baseline and for 5 days of the study. Other endpoints include portion of long PVCs that are able to ensure blood draw up to 5 days postoperatively, time needed to insert PVC in each group, reinsertion of PVC needed in both groups for any reason. All this data is recorded in the study protocol.

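### The secondary failure rate has two incompatible definitions in the same paragraph, one of them inverted, and its event and time origin also vary between sections

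*Protocol article*

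**What the plan says.** The Protocol article names one secondary endpoint. Its statistical section {20a} describes that endpoint twice in a single paragraph.

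- Opening sentence of {20a}: "failure rate is defined as the proportion of cannulas requiring reinsertion within 5 days after insertion".
- Later in the paragraph: "the failure rate is calculated from the ratio of cannulas that did not fail to cannulas that failed for any reason in each group", with the window "up to the first 5 days postoperatively".

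The same paragraph fixes the reporting format: "Primary and secondary outcomes will be reported as frequencies and percentages".

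Other sections bear on the event:

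- Outcomes {12} lists the "proportion of cannulas that requires reinsertion" among the recorded items, which matches the opening sentence of {20a}.
- The Abstract (Methods) says: "The secondary endpoint is a failure rate of the peripheral venous cannula to administer intravenous therapy up to 5 days postoperatively". Objectives {7} uses the same event and the same postoperative window.
- Reinsertion also stands as an endpoint of its own. {20a} lists "reinsertion of PVC needed in both groups for any reason" among the other endpoints, and the Abstract and {7} list it as tertiary.

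Section {18b} ends follow-up at 5 days or at hospital discharge, whichever is earlier.

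**The concern.** The first definition is a proportion between 0 and 1 that rises with failure. The second, as written, is the odds of not failing: it runs from 0 upwards without limit and falls as failure becomes more common. An analyst cannot follow both. One who follows the second would report the arm with the more durable cannulas as having the higher failure rate.

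The two sentences also count different things. A cannula that stops working when no further access is needed has failed, and can no longer deliver therapy, but does not require reinsertion. Discharge before day 5 makes such cases plausible. The clock starts at insertion in one sentence and is postoperative in the other.

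This is the trial's only secondary endpoint, and the article presents cannula durability as a strength of the study. The trial is unblinded, so an event left open could be settled after results have been seen.

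**Working it through.** The plan gives no assumed rate for this endpoint, so there is no figure of its own to reproduce. The check is algebra with illustrative rates.

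**1. The two formulas.** Let f be the proportion of cannulas that fail in an arm.

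- Definition 1: failed / all = f.
- Definition 2: non-failed / failed = (1 − f) / f.

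| f | Definition 1 | Definition 2 |
|---|---|---|
| 5% | 0.05 | 0.95/0.05 = 19.0 |
| 10% | 0.10 | 0.90/0.10 = 9.0 |
| 20% | 0.20 | 0.80/0.20 = 4.0 |
| 40% | 0.40 | 0.60/0.40 = 1.5 |
| 50% | 0.50 | 0.50/0.50 = 1.0 |
| 63% | 0.63 | 0.37/0.63 = 0.59 |

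The 63% is the upper failure rate cited in {6b}; the other values of f are assumptions. Definition 2 falls throughout as f rises, and at f = 0 it divides by zero. The two agree only where f = (1 − f)/f, that is f² + f − 1 = 0, so f = (√5 − 1)/2 ≈ 0.618.

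**2. A comparison between arms (assumed: 40 of 100 control and 20 of 100 ultrasound cannulas fail).**

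- Definition 1: 0.40 vs 0.20; ratio ultrasound to control 0.20/0.40 = 0.50.
- Definition 2: 60/40 = 1.5 vs 80/20 = 4.0; ratio 4.0/1.5 = 2.67.

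Both describe the same data, with ultrasound better. Under the label of failure rate, however, the second reads the opposite way.

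**3. Effect of the inversion on the planned chi-square test.** The statistic is N(ad − bc)² divided by the product of the four margins. With failed first, ad − bc = 40×80 − 60×20 = 2000. With non-failed first, it is 60×20 − 40×80 = −2000. The square and the margins are the same, so in both cases the statistic is 200 × 2000² / (100 × 100 × 60 × 140) = 9.52. The p-value does not move.

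**4. Effect of the event and the window.** Suppose F cannulas in an arm fail for any reason and k of them are not replaced because access is no longer needed. The count is F under any-reason failure and F − k under reinsertion. If k differs from zero, the 2×2 table changes, and with it the statistic. The time origin acts in the same way on failures near the end of the window. According to {11a} and {16a} the cannula is placed before surgery on the day of surgery, so the two origins should lie close together and the event probably matters more. The documents give no basis for a value of k.

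**The case against.** The strongest reply is that the intended meaning is clear. The opening sentence of {20a} is the one phrased as a definition, {12} agrees with it, the test is a chi-square on counts, and a value such as 4.0 is not a percentage. The ratio sentence may then be loose wording for a comparison of failed with non-failed cannulas. This is plausible, but the text does not say so, and reading the sentence charitably does not settle which event is counted or from when.

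Two stronger readings are tempting and should not be drawn.

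- *That the inversion changes the test result.* It does not. For one fixed event, exchanging failed and non-failed leaves the chi-square statistic and p-value as they were.
- *That replacement cannulas enter the analysis, so that correlated observations make the confidence intervals too narrow.* No section puts replacements in the denominator. {11c} describes the intervention as one unrepeated procedure, and {20a} treats the number of cannulas used as a separate variable, so the first cannula is a natural reading. Both definitions do count cannulas and neither excludes replacements, so independence would be in doubt only if replacements were counted.

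It is also fair to say that the overlap between reinsertion as the secondary event and reinsertion as a tertiary endpoint is redundancy, not an analytic error. It is a symptom of the unsettled event.

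**Conclusion.** The point holds within limits. {20a} states two definitions of the secondary endpoint that cannot both be followed, and the second is inverted as written. With the assumed 40% and 20%, the between-arm ratio is 0.50 under one and 2.67 under the other. That harm is confined to the reported estimate, its direction and its label.

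The part that can reach the test is the mismatch of events (reinsertion in {12} and {20a}, failure for any reason in {20a}, inability to give intravenous therapy in the Abstract and {7}) and of time origins (insertion or postoperative). Its size cannot be derived from the documents.

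The primary endpoint is untouched, and so is the sample size, which rests on unsuccessful insertion. This should be fixed before the data are analysed, but it does not threaten the trial.

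**What to change.** In {20a}, delete the ratio sentence and define the failure rate as failed / total in each group, reported as a percentage. Then:

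- Use one event throughout. Inability to give intravenous therapy through the cannula is the one that matches Objectives {7}; reinsertion then remains the separate tertiary endpoint, and {12} should be worded to agree.
- Choose one time origin and use it in the Abstract, {7} and {20a}.
- State how a patient discharged before day 5 with a working cannula is counted, since {18b} ends follow-up at discharge.
- Count the first study cannula once per patient, which secures the independence that the chi-square test needs. Say also whether an unsuccessful insertion, which {11b} can record as a failure, belongs to this endpoint.

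The cost is a few sentences, plus the registry update and ethics notification that {25} foresees for important changes. {20a} says the data come from the patient form. That form (Fig. 2) is not shown, so confirm that it records loss of function separately from replacement.

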## Interventions

### Explanation for the choice of comparators {6b}

Classic palpation approach for vascular access is challenging in DIVA patients. Up to 50% of orthopedic patients are DIVA [1, 2] and orthopedic surgeries are on the rise in developed countries. Medical staff can site venous cannula only to veins they can see. Therefore, the cannula is often in a suboptimal place of flexion of the arm in the wrist or elbow which are associated with complications [6, 7] and higher failure rates up to 63% [8].

Ultrasound enables us to place the cannula in an ideal place, in terms of the complications mentioned above. In addition, we can measure the diameter of the vein and use cannula width that will obscure only one third of the internal lumen. This should allow for blood draw because of undisturbed bloodstream in the vein.

We chose the UGVA approach in comparison to the classic palpation approach in standard clinical settings. This design of study allows to compare the standard of care (insertion of cannula by palpation) to the modern (ultrasound-guided insertion of cannula), technically more challenging but also a more rewarding option.

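### Section {20a} defines the secondary endpoint's failure rate in two incompatible ways, and one of them is inverted

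*Protocol article*

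**What the plan says.** Both statements are in the Protocol article, section Statistical methods for primary and secondary outcomes {20a}.

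- The opening sentence, in parentheses: "failure rate is defined as the proportion of cannulas requiring reinsertion within 5 days after insertion".
- Later, where the secondary endpoint is made operational: "the failure rate is calculated from the ratio of cannulas that did not fail to cannulas that failed for any reason in each group", over the first 5 postoperative days.

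The same section adds: "Primary and secondary outcomes will be reported as frequencies and percentages". It plans a chi-square test for the endpoint. The only risk ratio it mentions is for successful cannulation.

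Elsewhere, the abstract's Methods paragraph gives no formula: "The secondary endpoint is a failure rate of the peripheral venous cannula to administer intravenous therapy up to 5 days postoperatively". Explanation for the choice of comparators {6b} uses the term as a percentage where a larger value is worse, citing "higher failure rates up to 63" per cent.

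**The concern.** A failure rate should rise when more cannulas fail. The second statement divides the cannulas that survived by those that failed, so it falls when more fail. It is also not a proportion: it exceeds 1 whenever fewer than half of the cannulas fail, and it cannot be calculated when none fail.

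This endpoint carries the trial's durability question, which is whether ultrasound-placed long cannulas stay usable for 5 days. If an analyst followed the second sentence as written, the arm with fewer failures would be listed with the higher failure rate, and any ratio between arms would point the wrong way. The two statements also differ in the event they count and in when the 5 days start. Turning the ratio round would therefore not by itself make them agree.

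**Working it through.** The protocol gives no figure to reproduce here, so the check is algebraic.

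**Formulas.** Let p be the proportion of cannulas in an arm that fail.

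- First statement: failed / all = p.
- Second statement: not failed / failed = (1−p)/p.

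**Range of p.** No failure rates are assumed for this endpoint, so a range is shown. The 63% is the upper literature figure in {6b}. It refers to cannulas at flexion sites and is not a planning value for either arm.

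| p (first statement) | (1−p)/p (second statement) |
|---|---|
| 0% | undefined |
| 5% | 0.95/0.05 = 19.0 |
| 10% | 0.90/0.10 = 9.0 |
| 20% | 0.80/0.20 = 4.0 |
| 50% | 0.50/0.50 = 1.0 |
| 63% | 0.37/0.63 = 0.59 |
| 80% | 0.20/0.80 = 0.25 |

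The second column falls as the first rises, so the order of the arms always reverses.

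**Two-arm illustration** (assumed: 100 cannulas per arm, 20 failed with palpation, 10 with ultrasound).

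- First statement: 20% against 10%. RR of failure, ultrasound against palpation: 0.10/0.20 = 0.50.
- Second statement: 80/20 = 4.0 against 90/10 = 9.0. Ratio of ultrasound to palpation: 9.0/4.0 = 2.25.
- The 2.25 is the inverse of the odds ratio of failure: (10/90)/(20/80) = 0.444, and 1/0.444 = 2.25. Both the direction and the scale differ from the RR of 0.50.

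**Effect on the test.** Chi-square without continuity correction = 200 × (20×90 − 80×10)² / (100 × 100 × 30 × 170) = 200 × 1,000² / 51,000,000 = 3.92. Exchanging the failed and not-failed columns leaves this unchanged, so the p-value does not depend on orientation.

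**Other differences between the two statements.**

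- Event: the first counts cannulas that have to be replaced, the second those that failed for whatever reason. The abstract has a third wording, inability to deliver intravenous therapy. The abstract and Objectives {7} also list reinsertion separately as a tertiary outcome, so reading the secondary endpoint as reinsertion makes it overlap with that one.
- Clock: the first counts from insertion, the second from surgery. Insertion takes place before surgery, on the same day ({11a}, {16a}), so this gap is probably short. It still needs to be fixed for failures near the 5-day limit.

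**The case against.** The strongest reply is that the right definition is already there, comes first, and is the one worded as a definition. The percentage format fits only that version, and {6b} uses the term in the ordinary sense. To publish a reversed table, the authors would have to overlook all three. This stands, and it limits the point. A reader might infer that the endpoint has only an upside-down formula and that the ultrasound arm will be reported as worse. The documents do not support that: they contain one correct and one incorrect statement, and they do not say which prevails.

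Secondly, the chi-square test is indifferent to orientation. This also stands, so the planned p-value is not in question. But a p-value does not show which cannula lasts longer, and the direction and size of the difference are what the inverted sentence puts at risk.

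Thirdly, calculated from a ratio need not mean equal to it. With r the non-failed-to-failed ratio, 1/(1+r) recovers the proportion: 1/(1+4.0) = 20% and 1/(1+9.0) = 10%. That is arithmetically sound, but the protocol states no such conversion.

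Finally, any stated size is constructed, since the protocol gives no expected failure rates. That is so. The reversal itself holds for every pair of unequal rates at which the ratio is defined.

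**Conclusion.** The point holds as an internal contradiction: section {20a} gives two incompatible versions of the secondary endpoint, and the one that says how to calculate it is inverted. If that sentence is applied literally, the arm with fewer failures gets the higher value (4.0 against 9.0 for assumed failure of 20% against 10%), and an arm without failures has no value. The hypothesis test is unaffected. The reported value, its direction and the effect size are exposed. How likely a reversed report is cannot be judged from the documents. The correct definition and the percentage format make it avoidable, but an endpoint rule should not depend on the analyst noticing the slip. Even with the orientation corrected, the event and the time origin remain unsettled between the two statements.

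**What to change.** Delete the non-failed-to-failed ratio and keep one definition in {20a}:

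- Failure proportion = failed study cannulas / all study cannulas placed in the arm, with one index cannula per patient, analysed as randomised.
- State one event. The sponsor should choose between need for reinsertion, failure for any reason and inability to give intravenous therapy, and use the same wording in the abstract, Objectives {7} and {20a}.
- State one time origin for the 5 days, either insertion or surgery.
- Report n/N and % per arm, with the RR of failure for ultrasound against palpation and its 95% CI, noting that a value below 1 favours ultrasound. The chi-square test can stay.

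The cost is a sentence or two in the protocol and matching wording in any analysis plan. No additional patients or data collection are needed. Trial status describes the first randomisation as still to come, so on that timetable the text could be corrected before any outcome data exist.

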## Introduction

### Background and rationale {6a}

There is a group of patients with difficult intravenous access (DIVA). In experts’ hands, ultrasound-guided vascular access appears to be a significantly better method. Investigators hypothesize that UGVA is superior also in short-term patency of cannula for up to 5 days and even for blood draw through cannula. In overweight/obese orthopedic patients the DIVA subpopulation can reach up to 50% [1, 2]. Ultrasound seems to facilitate vascular access in patients with higher BMI [3]. The classic landmark technique becomes very difficult in the higher BMI ranges, whereas ultrasound is mostly unaffected by BMI [4]. In our hospital, we perform over 1.000 joint arthroplasties annually. In a small internal hospital audit (*n* = 34) we found out that 60% of inserted cannulas that adhered to strict insertion protocol (Fig. 1) under ultrasound, ensured blood draw on POD (post operative day) 1 and 2. If we can insert a low-cost long PVC that can last up to 5 days and allows for blood drawing, it will ease the perioperative period for DIVA patients and medical staff as well. To the best of our knowledge, no randomized controlled trials have yet been performed to study the effect of ultrasound-guided vascular access of long PVCs in orthopedic overweight patients with focus on i.v. access patency up to 5 days and the ability to draw blood through PVC. Ultrasound can reduce the number of attempts and complications as well, but only in the experienced hands of a fully trained UGVA specialist. Repeated cannula insertions not only put a lot of stress on patients and medical staff. They also waste OR (operating room) time and use up the veins of the patient, which may never heal [5] and this makes vein punctures even more difficult in the future.

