### Objectives {7}

The primary objective of this investigator-initiated prospective randomized controlled trial is to compare the number of attempts for ultrasound-guided insertion of PVC with common palpation insertion of PVC in overweight/obese patients. The secondary objective is the comparison of long PVCs and “regular” short PVCs in terms of their ability to administer intravenous therapy through the cannula up to 5 days postoperatively. Tertiary objectives are a portion of long PVCs that are able to ensure blood draw up to 5 days postoperatively, time needed to insert PVC in each group, number of needle tip redirections in both groups, and reinsertion of PVC needed in both groups for any reason.

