### Participant timeline {13}

**Table Tabb:** 

	Study period					
	Enrolment	List of patient time period	Allocation	Post allocation		Close out
Timepoint	Day − 1	Day – X	0	Day 1	Day 2–4	Day 5
Enrolment:						
Eligibility screen	X					
Informed consent	X					
Randomization		X				
Allocation			X			
Interventions:						
Group C				X		
Group USG				X		
Assessments:						
Baseline variables				X		
Primary outcome				X		
Secondary outcome					X	X

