## Assignment of interventions: allocation

### Sequence generation {16a}

A random sequence of numbers is generated using SPSS software v. 20.0 (IBM SPSS, Armonk, NY), and this is translated to a series of opaque envelopes which will be used to allocate eligible participants to groups once they have satisfied the inclusion criteria. On the day of surgery, in the block room, the anesthetist will open the envelope and find out the allocation of the patient. According to patient allocation, medical staff will perform the procedure in accordance with the study protocol. This procedure will be repeated until the target sample size is reached.

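### The A-DIVA score is listed as a tertiary outcome to be tested between arms; it should be a baseline characteristic, recorded before the envelope is opened and usable as a covariate

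*Protocol article*

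**What the plan says.** **Role of A-DIVA.** In Statistical methods {20a} the score is in the tertiary analysis, among the items on which the arms are compared: "time required for cannula insertion, number of cannulas used, A-DIVA scoring system, etc", by t-test or Mann–Whitney U test. Objectives {7} begins its tertiary list differently: "Tertiary objectives are a portion of long PVCs that are able to ensure blood draw up to 5 days postoperatively". That list goes on to insertion time, needle tip redirections and reinsertion. The abstract gives the same four items. Neither names A-DIVA.

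**Timing.** Participant timeline {13} marks eligibility screening at Day −1 and allocation at 0. The row "Baseline variables" is marked once, at Day 1 under post allocation, in the same column as both interventions and the primary outcome. Sequence generation {16a} adds: "On the day of surgery, in the block room, the anesthetist will open the envelope and find out the allocation of the patient". Implementation {16c} says that patient and researcher both learn the allocation, and section {17a} that nobody is blinded.

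**Primary analysis.** Section {20a} sets a chi-square "test in terms of the difference in approaches of cannula insertion between groups in the number of punctures" and adds "RR and 95% confidence interval of successful venous cannulation will be also calculated". It names no covariate, and {16a} mentions no stratification. Background {6a} nevertheless identifies a prognostic factor: "The classic landmark technique becomes very difficult in the higher BMI ranges, whereas ultrasound is mostly unaffected by BMI".

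**The concern.** A patient's access difficulty exists before the needle is picked up. Background {6a} treats it that way, speaking of a group of patients who have it. If such a score is tested between randomised arms as an outcome, a small p-value says nothing about ultrasound guidance, yet it could be reported as a tertiary result.

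Timing adds to this. If the score is taken after the envelope is opened, the person scoring may know the arm. A score recorded that way is a weaker description of the sample and a weaker covariate, and no later analysis can repair it. Section {20a} also plans paired tests that use baseline data, so the integrity of baseline matters beyond a descriptive table.

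Finally, once the score is filed as an outcome, it is not available to the primary comparison as a prognostic covariate, which is where it could be useful.

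**Working it through.** **1. Text comparison.**

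| Item | Where | What it shows |
|---|---|---|
| A-DIVA in the tertiary tests | {20a} | compared between arms |
| Tertiary lists | Abstract, {7} | A-DIVA absent |
| Difficult access | {6a}, {6b} | attribute of the patient |
| Baseline variables | {13} | Day 1, after allocation at 0 |
| Knowledge of arm | {16a}, {16c}, {17a} | open from the time the envelope is opened |
| BMI | {10}, {13} | eligibility criterion, screened at Day −1 |

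The classification problem and the inconsistency between lists follow directly. The timing concern reaches A-DIVA only if the score is among the baseline variables taken at Day 1. It cannot reach BMI, which must be known at Day −1.

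**2. The plan's own sample size.** Inputs from {14}: failure 20% against 5%, α 0.05, power 90%, total 162, raised by 20% and rounded to about 200. Equal arms are assumed, since the ratio is not stated. With pooled variance,

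n per arm = [z(α)·√(2p̄q̄) + z(β)·√(p₁q₁ + p₂q₂)]² / (p₁ − p₂)²

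p̄ = 0.125, √(2 × 0.125 × 0.875) = 0.4677, √(0.16 + 0.0475) = 0.4555.

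- One-sided: (1.645 × 0.4677 + 1.282 × 0.4555)² / 0.0225 = 81.4, so 82 per arm, 164 in total, close to 162.
- Two-sided: (1.960 × 0.4677 + 1.282 × 0.4555)² / 0.0225 = 100.1, so 101 per arm, 202 in total.

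Inflation: 162 × 1.2 = 194.4, consistent with about 200. Sidedness is a separate matter. These figures only set the two sizes used next, 81 and 100 per arm.

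**3. What adjustment would gain.** The covariate's strength is not in the protocol, so it is assumed: odds ratio 1.5, 2 or 3 per SD for first-insertion failure, with marginal risks held at 20% and 5%. Each scenario has 1,500 simulated trials. The two-sided Pearson test is compared with the likelihood-ratio test for arm in a logistic model containing the covariate. Monte Carlo standard error is about 0.01 per power figure.

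| Covariate acts in | OR per SD | 81 per arm: unadjusted → adjusted | 100 per arm: unadjusted → adjusted |
|---|---|---|---|
| both arms | 1.5 | 0.840 → 0.851 | 0.921 → 0.925 |
| both arms | 2 | 0.856 → 0.871 | 0.915 → 0.933 |
| both arms | 3 | 0.849 → 0.893 | 0.929 → 0.955 |
| palpation arm only | 1.5 | 0.849 → 0.853 | 0.923 → 0.925 |
| palpation arm only | 2 | 0.831 → 0.846 | 0.924 → 0.931 |
| palpation arm only | 3 | 0.847 → 0.864 | 0.912 → 0.927 |

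The gain is 0.4 to 4.4 points in the first case and 0.2 to 1.7 in the second. The second is what {6a} suggests for BMI. The change of test statistic explains almost none of it: summing exact binomial probabilities over all 2×2 tables without a covariate gives Pearson 85.4% and likelihood ratio 85.8% at 81 per arm, and 92.1% for both at 100.

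**4. Information available.** Expected failures at 100 per arm: 100 × 0.20 + 100 × 0.05 = 20 + 5 = 25. Arm plus two covariates gives 25 / 3 ≈ 8 events per parameter.

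**The case against.** The strongest case on the other side has four parts.

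- **A-DIVA is undefined in the article and its form is not shown.** It is therefore unknown when the score is taken, by whom, and how much judgement it involves. This stands. A reader might infer that the score is judgement-based and taken late; the document states neither.
- **The timeline is schematic.** The Day 1 column may simply group everything done around the procedure, and it gives no order within the day. This also stands in part: the table does not prove that baseline follows the envelope. But its only mark for baseline lies after allocation, so as written it does not protect the score.
- **An unadjusted chi-square is valid under randomisation, and an analysis plan not shown may add covariates.** Correct. A reader might infer that ignoring A-DIVA and BMI makes the primary analysis wrong; it does not. A reader might also extend the timing concern to BMI, but screening at Day −1 rules that out.
- **The consequence is one superfluous p-value, and a model with few events has its own risks.** The first half is fair as to the primary and secondary conclusions, which the tertiary test leaves untouched. The second half is a reason to keep the model sparse and to report the simple test with it.

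The misclassification in {20a} and its disagreement with the abstract and {7} survive all four.

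**Conclusion.** The point holds in limited form. Section {20a} treats a patient characteristic as an outcome to be tested, contrary to the protocol's own tertiary lists; this rests on the text, together with the reading that difficult access precedes and is not altered by the technique. The timeline leaves open that A-DIVA is scored with the arm known; this is conditional on the score being taken at Day 1.

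Adjustment is a cheap improvement and not a correction. Its size, about 0 to 4 points of power, depends on assumed odds ratios of 1.5 to 3 per SD and on the protocol's failure risks of 20% and 5%. It is nearer 0 to 2 points if the covariate matters only for palpation.

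**What to change.** 1. State that A-DIVA is recorded before the envelope is opened, and move the baseline mark in {13} ahead of allocation.
2. Remove A-DIVA from the tertiary comparisons in {20a}, which brings that section into line with the abstract and {7} on this item. Report it by arm in the baseline table without a test.
3. Prespecify an analysis of the primary comparison adjusted for A-DIVA, with BMI as at most one further covariate, giving a standardised risk difference or risk ratio. If events are too sparse, use Mantel–Haenszel by A-DIVA class. Report it together with the unadjusted chi-square.

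The cost is a few lines of text, a possible change in the order of the form, and one extra model. The first item has to be in place before a patient is allocated, because it cannot be recovered afterwards. The limit on the third is the event count, about 25 in all and about 5 in the ultrasound arm, which is why the model should carry no more than two covariates.
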